### Statistical Analysis

#### Power

The focus of this project is to test feasibility; thus, for phase 1, we will recruit based on existing recommendations for feasibility studies (ie, N≥30) [58]. However, we will maximize sample size for robust EMA data in phase 2. Specifically, for phase 2, the purpose is to examine factors that influence sustained intervention effects. We anticipate that all individuals who complete postintervention data collection (n=64; 32 each year, 80% retention) will begin EMAs. Per past EMA studies, we estimate 75% compliance with EMAs. For questions only asked in the morning daily diary (eg, sleep), each participant will complete approximately 21 daily diary responses (1 per day × 28 days × 0.75 compliance). Thus, with an effective sample size of 237 based on a conservatively high estimate of the correlation between daily assessment of sleep (0.7 × 1344 EMA responses), we will have 80% power to detect an association of a relatively small effect size (Cohen *f*^2^=0.034) between sleep and fiber intake. When examining associations between fiber intake and momentary predictors, which are assessed multiple times per day (eg, stress), we will be able to detect even smaller effect sizes.

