## Methods

### Study Design

On the basis of our primary study outcome (feasibility), we will conduct a 2-phase single-arm study [42,43] to preliminarily test our mHealth-based fiber intervention in up to 80 young adults with prediabetes (phase 1) and elucidate factors that impact sustained behavior change and fiber intake after intervention end using EMAs (phase 2) (Figure 1).

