#### Analytic Plan

For phase 1, we will compute descriptive statistics (for all feasibility metrics) and 2-tailed paired *t* tests to examine changes in our preliminary efficacy outcomes (fiber intake, HbA_1c_, and HOMA-IR) from baseline to the postintervention time point as a measure of preliminary efficacy. For phase 2, the primary goal is to determine whether participants maintain fiber intake after the intervention and identify real-time factors that predict adherence. Adherence will be defined as maintaining fiber intake at or above 80% [59] of postintervention levels based on ASA-24 data at the start and end of the 4-week EMA period. A logistic multilevel model will be used to predict adherence (1=maintained; 0=dropped below threshold) from EMA-measured factors (eg, affect). EMA predictors will be aggregated at the participant level (eg, mean stress across the EMA period) to assess overall exposure to these factors, whereas daily fluctuations will be modeled using within-person deviations from each participant’s mean. To assess how the influence of these predictors changes over time, we will use time-varying effect modeling, allowing for the examination of whether certain factors (eg, stress) exert stronger effects on adherence early vs late in the observation period. Additionally, we will explore the role of EMA variability, calculating within-person fluctuations (eg, SD of stress) to test whether greater instability in these factors predicts lower adherence. We will assess patterns of missing data and conduct sensitivity analyses assuming different missing data mechanisms. For example, we will consider a multiple imputation approach, which uses baseline characteristics to account for potential missing at random mechanisms [60,61].

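### The 80% power stated for phase 2 needs a daily fiber outcome, but the analytic plan's only phase 2 outcome is one adherence value per participant

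*Protocol article*

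**What the plan says.** The Power section of the protocol article sizes phase 1 by a feasibility convention (at least 30 participants) and then says the sample will be maximized for phase 2 EMA data. For phase 2 it states: "We anticipate that all individuals who complete postintervention data collection (n=64; 32 each year, 80% retention) will begin EMAs". It assumes 75% compliance, so that "each participant will complete approximately 21 daily diary responses (1 per day × 28 days × 0.75 compliance"). The total is 1344 responses. With a correlation of 0.7 between daily sleep assessments this becomes an effective sample size of 237, from which the section concludes that "we will have 80% power to detect an association of a relatively small effect size", f² = 0.034, for sleep and fiber intake. It adds that still smaller effects can be detected for predictors measured several times a day.

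The Analytic Plan section sets the phase 2 outcome: "Adherence will be defined as maintaining fiber intake at or above 80" percent of the postintervention level, judged from ASA-24 data at the start and end of the 4-week period and coded 1 or 0. A logistic multilevel model predicts this adherence from EMA factors. They enter as participant means, within-person daily deviations and within-person SDs, and a time-varying effect model is added. Under Data Collection, Phase 2, the end measure is two ASA-24 recalls after the 4 weeks.

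**The concern.** The two sections describe different analyses. The power calculation treats diary days as the units that carry information about the association with fiber intake. The planned outcome is measured once per participant. More diaries make a participant's mean or SD of a predictor more precise, but they add no adherence outcomes. Within-person deviations do not help either, because the outcome does not vary within a person.

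Identifying real-time predictors of adherence is part of what the Analytic Plan calls the primary goal of phase 2. A reader who takes the stated 80% at face value could give null predictor results more weight than the design supports. Phase 2 data are also the only reason the Power section gives for recruiting beyond the feasibility minimum.

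**Working it through.** **Inputs from the protocol article.** Up to 80 enrolled (Study Design). 64 anticipated at the start of phase 2, that is 80 × 0.80; 28 days; 75% compliance; correlation 0.7; f² = 0.034 (all Power).

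**Assumptions.** Two-sided alpha of 5% and one predictor; the article states neither. Adherence rates of 50%, 70% and 80% for the binary outcome; the article gives none.

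**1. The stated figures.**
- Responses: 28 × 0.75 = 21 per person; 64 × 21 = 1344.
- Effective sample size, first-order autoregressive formula: 1344 × (1 − 0.7)/(1 + 0.7) = 237.2. This matches the stated 237.
- Power, noncentral F test with 1 and n − 2 degrees of freedom and noncentrality λ = f² × n: λ = 0.034 × 237 = 8.06, power 80.7%. The f² detectable with exactly 80% power is 0.0334. The stated 80% at 0.034 reproduces.

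**2. What that calculation presupposes.** It holds for a model in which each diary day contributes a fiber outcome alongside that day's sleep. The Analytic Plan contains no such model. Its outcome is adherence, one value per participant.

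**3. The same test with participants as the units.**

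| Independent outcomes | λ at f² = 0.034 | Power at f² = 0.034 | f² detectable with 80% power |
|---|---|---|---|
| 237 (stated basis) | 8.06 | 80.7% | 0.033 |
| 64 (anticipated) | 2.18 | 30.6% | 0.127 |
| 80 (all retained) | 2.72 | 37% | 0.101 |

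The detectable f² at n = 64 is about 0.127/0.034 = 3.7 times the stated value. With r² = f²/(1 + f²), the correlation is about 0.34 instead of 0.18. About 233 independent outcomes would be needed for 80% power at f² = 0.034.

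**4. The planned outcome is binary.** Step 3 treats the outcome as continuous, so it is optimistic.
- A simulation at n = 64, with a latent outcome at f² = 0.034 split into yes/no, gave about 19% to 21% power (likelihood ratio test) or 16% to 18% (Wald test) for adherence of 50% to 80%.
- Detectable log odds ratio per SD of the predictor with 80% power: β = (1.960 + 0.842)/√(64 × p × (1 − p)).
  - p = 0.5: 2.80/√16 = 0.70, odds ratio 2.0
  - p = 0.7: 2.80/√13.44 = 0.76, odds ratio 2.1
  - p = 0.8: 2.80/√10.24 = 0.88, odds ratio 2.4

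**5. Predictors measured several times a day.** Three prompts a day instead of one still leave one adherence value per participant. The statement that smaller effects become detectable therefore fails for the same reason.

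**The case against.** The strongest reply is that a daily analysis is foreseen. The Analytic Plan specifies a multilevel model, within-person deviations and time-varying effects. The morning diary includes a checklist of high-fiber foods, and the Power section itself speaks of associations with fiber intake. A condensed article may leave the model details to a fuller plan. Part of this stands: daily-level predictors are planned, so it would be wrong to say that no daily analysis is foreseen. But the only outcome the Analytic Plan names is ASA-24 adherence, and the checklist is not named as an outcome. The point is therefore not missing detail; a stated power figure does not fit the stated outcome.

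A reader might infer stronger things that the article does not support:
- That the power arithmetic is wrong. It reproduces.
- That 31% is the power of the planned logistic analysis. It is a continuous-outcome approximation, and the binary outcome has less power.
- That 64 is a ceiling. It is the number anticipated at 80% retention; up to 80 may be enrolled.
- That the study as a whole is undersized. The primary outcome is feasibility, and phase 1 is sized on that basis.
- That null results will be reported as evidence of no association. The article does not say so.

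**Conclusion.** The concern holds as a mismatch between the power statement and the planned analysis. The 80% power for f² = 0.034 does not belong to the adherence analysis. With one outcome per participant, the continuous-outcome approximation gives about 31% power at that effect for 64 participants and 37% for 80, and 80% power only at f² of about 0.13 and 0.10 respectively. The binary outcome has less power, with a detectable odds ratio per SD of about 2.0 to 2.4 at n = 64. These figures rest on one predictor, a two-sided 5% alpha and adherence between 50% and 80%, all assumed. The conclusion does not depend on the exact values, because it follows from counting outcomes. Severity is moderate: the point concerns the phase 2 power statement in a study whose primary outcome is feasibility.

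**What to change.** Restate phase 2 power for the adherence analysis at the anticipated n = 64: 80% power for f² of about 0.13 under a continuous-outcome approximation, or for an odds ratio per SD of about 2.0 to 2.4 with the binary outcome. State the alpha, the number of predictors and the adherence rate assumed. Then either add to the Analytic Plan a named multilevel model with the daily high-fiber food checklist as outcome and attach the 237-based figure to that model alone, or delete that figure. Limit the sentence on predictors measured several times a day in the same way, or remove it.

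The cost is a rewritten power paragraph and, if the daily model is wanted, a short addition to the Analytic Plan. The checklist is already collected, and no extra enrolment is needed. The stated detectable effect becomes less favourable.

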#### Analytic Plan

For phase 1, we will compute descriptive statistics (for all feasibility metrics) and 2-tailed paired *t* tests to examine changes in our preliminary efficacy outcomes (fiber intake, HbA_1c_, and HOMA-IR) from baseline to the postintervention time point as a measure of preliminary efficacy. For phase 2, the primary goal is to determine whether participants maintain fiber intake after the intervention and identify real-time factors that predict adherence. Adherence will be defined as maintaining fiber intake at or above 80% [59] of postintervention levels based on ASA-24 data at the start and end of the 4-week EMA period. A logistic multilevel model will be used to predict adherence (1=maintained; 0=dropped below threshold) from EMA-measured factors (eg, affect). EMA predictors will be aggregated at the participant level (eg, mean stress across the EMA period) to assess overall exposure to these factors, whereas daily fluctuations will be modeled using within-person deviations from each participant’s mean. To assess how the influence of these predictors changes over time, we will use time-varying effect modeling, allowing for the examination of whether certain factors (eg, stress) exert stronger effects on adherence early vs late in the observation period. Additionally, we will explore the role of EMA variability, calculating within-person fluctuations (eg, SD of stress) to test whether greater instability in these factors predicts lower adherence. We will assess patterns of missing data and conduct sensitivity analyses assuming different missing data mechanisms. For example, we will consider a multiple imputation approach, which uses baseline characteristics to account for potential missing at random mechanisms [60,61].

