**Methods:**

This single-arm feasibility study includes 2 phases to preliminarily test an mHealth-based fiber intervention (phase 1) and elucidate factors that impact sustained behavior change and fiber intake after intervention end using ecological momentary assessment (EMA; phase 2). The intervention is 3 months in length and features daily EMAs with responsive text–based coping messages to target key predictors of fiber intake. EMAs will also be paired with brief (ie, <1 minute) educational videos on fiber delivered once per day. Participants will also receive weekly home-delivered high-fiber food packages and wear a continuous glucose monitor at 2 time points during the intervention as a form of biofeedback. At the baseline and postintervention time points, fasting blood glucose, hemoglobin A_1c_, and insulin resistance (Homeostatic Model Assessment of Insulin Resistance) will be assessed. After the postintervention time point, participants will continue with daily EMAs to assess factors associated with sustained fiber intake. Diet will be assessed using Automated Self-Administered 24-hour dietary recalls at the baseline and postintervention time point and after the phase 2 EMA.

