### Data Collection

#### Phase 1

Participants will complete 2 in-person data collection sessions at the University of Oklahoma Health Campus in Tulsa, one at baseline and one after the 3-month intervention (postintervention time point). Each time, they will be asked to fast for 10 hours and have a venous blood draw done, complete anthropometric assessments, and complete a measure of capillary fasting blood glucose. Venous blood samples will be collected and processed for assessment of fasting insulin. Fasting capillary blood glucose and venous insulin will be combined to calculate the Homeostatic Model Assessment of Insulin Resistance (HOMA-IR) using established calculations (fasting glucose in mmol/L × fasting insulin in μU/mL/22.5) [53,54]. If no HbA_1c_ value is on file for the previous 3 months, HbA_1c_ will be checked using an A1CNow Self Check system (PTS Diagnostics), which will be rechecked at the postintervention time point. On 2 random days after completing the baseline visit, participants will also complete 2 separate Automated Self-Administered 24-hour dietary recalls (ASA-24) to quantify fiber intake. They will also complete surveys, including a measure of basic demographic variables. Surveys will be administered in REDCap [55,56].

During the intervention period, participants will complete daily EMAs on the Insight mHealth app maintained by the University of Oklahoma Health Campus OU Health Stephenson Cancer Center mHealth Shared Resource. This will include a run-in period, where the Insight app will deliver a morning daily diary, a midmorning diary, and a midday diary. This will decrease to only a morning daily diary during the intervention period. The morning daily diary is delivered 30 minutes after waking, before typical morning mealtimes. The midmorning and midday EMAs will be delivered approximately 2 hours after normal first and second mealtimes for the day. The morning daily diary will include a checklist-type assessment of intake of high-fiber foods and static measures such as sleep, whereas all daily diaries will assess affect, food cravings, digestive symptoms, feelings of “lack of time,” motivation to eat high-fiber foods, and urge to eat tasty food. Participants will also be presented with participant-initiated questions on the app to report when a study-provided food was eaten.

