To assess feasibility of the intervention, we will evaluate the following metrics according to Bowen et al [57]: implementation, demand, acceptability, and preliminary efficacy. Implementation will be assessed via review of message delivery, which will be automatically tracked on Insight. We will also track delivery of high-fiber food packages and CGM provision as defined in the protocol. For demand, we will assess participant retention in the trial as reflected by completion of data collection activities, as well as intervention uptake. Intervention uptake will be assessed via the percentage of all delivered content viewed by participants on Insight, use of CGMs by participants for the total duration requested, and participant report of consumption of provided high-fiber foods. For acceptability, we will provide acceptability surveys at the postintervention time point that include Likert-scale questions. Finally, for preliminary efficacy, we will leverage data collection on HbA_1c_ and the HOMA-IR.

#### Phase 2

After completion of the intervention and phase 1 postintervention data collection, participants will begin an observation-only period of EMA that spans 4 weeks. During this time, they will receive no intervention but complete EMAs 3 times a day as in the run-in period. EMA variables will be the same as during phase 1. Then, after completion of this period, they will repeat 2 more random, unannounced ASA-24 measures for fiber intake (“post-observation” time point).

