### Limitations

While this study is innovative, it is not without limitations. First, as a single-arm trial, the effects of the intervention cannot be fully ascertained. Future work should include randomized trials, including comparators that feature either standard-of-care guidance (eg, DPP) or alternative diets that tap into the same psychosocial mechanisms via different dietary targets (eg, ketogenic or carnivore diet). These future trials should include more robust measures of glucose homeostasis, including oral glucose tolerance tests. Additionally, while participants are provided with food in this study, it is not a full outpatient feeding trial wherein all food is provided. This introduces variability; however, we are seeking to assess this variability in part via EMA, which could result in an intervention with greater ecological validity and potential for long-term effectiveness.

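### The phase 2 maintained/dropped outcome is an 80% cut on a ratio of short recall means, with no allowance for day-to-day variation; the continuous log ratio from the same recalls would serve better

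*Protocol article*

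**What the plan says.** The Analytic Plan gives phase 2 its purpose: "the primary goal is to determine whether participants maintain fiber intake after the intervention and identify real-time factors that predict adherence". It then sets the outcome: "Adherence will be defined as maintaining fiber intake at or above 80% [59] of postintervention levels based on ASA-24 data at the start and end", where the period meant is phase 2. The label enters the model directly: "A logistic multilevel model will be used to predict adherence (1=maintained; 0=dropped below threshold) from EMA-measured factors". The same section also plans within-person deviations, time-varying effect modelling and within-person SDs as predictors, all directed at adherence.

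On the number of recalls, Data Collection states for the end of phase 2 that "they will repeat 2 more random, unannounced ASA-24 measures for fiber intake". For baseline, "participants will also complete 2 separate Automated Self-Administered 24-hour dietary recalls (ASA-24) to quantify fiber intake". The abstract confirms a postintervention measurement: "Diet will be assessed using Automated Self-Administered 24-hour dietary recalls at the baseline and postintervention time point and after the phase 2 EMA". No count is given for that time point. Two is the natural inference from the baseline scheme and from the wording about repeating two more.

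The nearest remark on variability is in Limitations, about participants not receiving all their food from the study: "This introduces variability; however, we are seeking to assess this variability in part via EMA". It gives no figure and does not concern measurement error in the label.

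**The concern.** Each participant gets one label, from a hard cut that tolerates only a 20% fall between two short-term means. What a person eats on two sampled days differs from habitual intake. A participant who happens to eat lentils on a sampled day at the postintervention point, and not on a sampled day four weeks later, can fall below the cut with habitual intake unchanged. The reverse also happens: a true fall can be hidden by two good days.

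Both parts of the phase 2 goal depend on the label. The share reported as maintaining intake may differ from the true share. Associations between EMA factors and maintenance are diluted, because some zeros and ones reflect which days were sampled. The plan's missing-data provisions do not address this, since the recalls are present but imprecise.

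**Working it through.** **1. The plan's own phase 2 figure.** The Power section expects "n=64; 32 each year, 80% retention", with 1 × 28 × 0.75 = 21 diary responses each: 64 × 21 = 1344. With a correlation of 0.7 between successive days, 1344 × (1 − 0.7)/(1 + 0.7) = 237.2, which reproduces the stated 237. Power at f² = 0.034 (two-sided 5% assumed) is then 0.807, in line with the stated 80%. That figure concerns a daily association between sleep and fiber intake. The maintained/dropped label has one value per participant, so at most 64, and no power is stated for it.

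**2. Inputs for the label.** Cut 0.80 (Analytic Plan); two recalls at the end (Data Collection, Phase 2); two at the start (inferred); 64 participants (Power). Assumed, because the documents do not give it: within-person CV of daily fiber from 0.20 to 0.60. Also assumed: lognormal intake, independent days, no reporting bias.

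**3. Unchanged participants labelled dropped.** The SD of the log ratio of two independent 2-day means is approximately √(2 × ln(1 + CV²/2)). The probability of falling below the cut with no true change is Φ(ln 0.8 / SD), with ln 0.8 = −0.223.

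| CV | SD of log ratio | P(labelled dropped) | of 64, if all unchanged |
|---|---|---|---|
| 0.20 | 0.199 | 13% | 8 |
| 0.30 | 0.297 | 23% | 14 |
| 0.40 | 0.392 | 28% | 18 |
| 0.50 | 0.485 | 32% | 21 |
| 0.60 | 0.575 | 35% | 22 |

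A normal approximation, Φ(−0.2/(CV × √(1.64/2))), gives 13.5% to 35.6% over the same range. Lognormal simulation gives 13.1% to 34.7%.

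**4. True falls that are missed.** For a true ratio of 0.60, P(labelled maintained) = 1 − Φ((ln 0.8 − ln 0.6)/SD) = 17%, 23% and 28% at CV 0.30, 0.40 and 0.50. A true fall to 50% is labelled dropped 99% of the time at CV 0.20 and 84% at CV 0.50.

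**5. The reported share when true change varies.** Take CV 0.40 and a true log ratio with SD 0.25 (both assumed). The observed log ratio has SD √(0.25² + 0.392²) = 0.465. The share maintained is Φ(ln(median/0.8)/SD), with 0.25 for the true share and 0.465 for the observed share.

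| Median true ratio | True share | Observed share | Difference |
|---|---|---|---|
| 0.85 | 60% | 55% | 4 points |
| 0.90 | 68% | 60% | 8 points |
| 1.00 | 81% | 68% | 13 points |

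**6. Predictor associations.** Illustrative simulation with n = 64, median true ratio 0.85, log-SD 0.25, and a participant-level predictor correlated 0.5 with true log change, tested two-sided at 5%. Power with an error-free label would be about 92%.

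| CV | Planned label | Continuous log ratio, same recalls |
|---|---|---|
| 0.20 | about 72% | about 90% |
| 0.30 | about 55% | about 75% |
| 0.40 | about 40% | about 58% |
| 0.50 | about 31% | about 46% |

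Two mechanisms are at work. Misclassification pulls the odds ratio towards 1. Dichotomising then discards how far above or below the cut each person lies. With the log ratio as outcome, random recall error unrelated to the predictor widens the confidence interval but does not bias the slope.

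**The case against.** The strongest reply is that every rate above rests on a CV and a spread of true change that the documents do not supply. That stands, and it is why ranges are given. A reader might take about a quarter of unchanged participants as the false-drop rate, but that fits only a CV of about 0.30 to 0.35.

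A reader might also infer that the label is mostly noise. The calculations do not show that. Across simulated populations (CV 0.20 to 0.50, median true ratio 0.8 to 0.9, log-SD 0.15 to 0.35) the label was right for about 62% to 84% of participants, and large falls were mostly detected. Nor does the count of 8 to 22 of 64 describe the expected bias in the reported share. It applies only if every true ratio is exactly 1; otherwise the two kinds of error partly cancel, as step 5 shows.

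It is also fair to say that feasibility is the study's primary outcome, that the 80% cut carries a citation not available here, and that usual-intake modelling of recalls is often left to a fuller document. The first lowers the weight of the point. The other two do not remove it: the article itself fixes the instrument, the cut, the end-point recall count and the model, and the choice of a dichotomised outcome is visible there.

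Finally, a continuous outcome leaves each person's recall error as large as before. That is true. The gain comes from not cutting the ratio and from averaging the error in a mean.

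**Conclusion.** The point holds as a cheap improvement to the phase 2 analysis. An 80% cut on a ratio of short recall means, with no allowance for day-to-day variation, would label about 13% to 35% of unchanged participants as dropped. This assumes CV 0.20 to 0.60, independent days and two recalls per end, of which the postintervention count is inferred. Bias in the reported share is smaller once true change varies: about 4 to 13 points in the illustration at CV 0.40. What matters more is the loss for the predictor question. In the illustrative setting, power is about 31% to 72% with the planned label and about 46% to 90% with the continuous ratio over CV 0.20 to 0.50. Correlated recall days or reporting bias would change these figures. Phase 1 feasibility is unaffected.

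**What to change.** Using the same recalls:

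- Make the phase 2 outcome the log ratio of post-observation to postintervention fiber. Report its mean, back-transformed to a percentage retained, with a confidence interval.
- Regress the log ratio on the participant-level EMA means and SDs.
- There is only one ratio per participant, so within-person deviations, which average to zero for each person, cannot explain it. For the within-person and time-varying models, use the fiber-food checklist in the morning daily diary as the outcome. Data Collection carries the same EMA variables into phase 2.
- Keep the 80% classification as a descriptive secondary figure, with a note that 2-day sampling error misclassifies individuals.
- State the number of postintervention recalls.

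The cost is wording in the analysis plan, with no added recalls or visits. There are two downsides. The headline becomes a mean percentage retained instead of a count of adherent participants. The daily models will describe reported high-fiber foods, not grams of fiber.

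### The phase 2 multilevel logistic model does not match its outcome: adherence is one yes/no status per participant, so daily-deviation effects and a random intercept cannot be estimated from it

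*Protocol article*

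**What the plan says.** All references are to the Protocol article.

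- **Outcome (Analytic Plan).** "Adherence will be defined as maintaining fiber intake at or above 80% [59] of postintervention levels based on ASA-24 data at the start and end". Start and end here refer to the 4 weeks of phase 2 observation. The postintervention level is the reference, and the result is coded 1 or 0.
- **Model (Analytic Plan).** "A logistic multilevel model will be used to predict adherence (1=maintained; 0=dropped below threshold) from EMA-measured factors (eg, affect". EMA predictors enter as participant-level averages, "whereas daily fluctuations will be modeled using within-person deviations" from the participant's own mean. For change over time, "we will use time-varying effect modeling", with the stated interest in whether a factor acts on adherence more strongly early or late in the period. The within-person SD of a factor is a further predictor.
- **Timing of recalls.** Data Collection, Phase 2: "Then, after completion of this period, they will repeat 2 more random, unannounced ASA-24 measures for fiber intake". The abstract's Methods agree: "Diet will be assessed using Automated Self-Administered 24-hour dietary recalls at the baseline and postintervention time point and after the phase 2 EMA". No recall falls inside the 4 weeks.
- **A daily diet measure exists (Data Collection, Phase 1).** "The morning daily diary will include a checklist-type assessment of intake of high-fiber foods". Phase 2 keeps the same EMA variables, but the definition of adherence does not use the checklist.
- **Power.** 64 participants with about 21 diary responses each give 1344 responses and an effective sample size of 237. This is said to give 80% power for f²=0.034 between sleep and fiber intake.

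**The concern.** A within-person effect is estimated by setting a participant's good days against the same participant's bad days. That requires an outcome that differs between those days. Here the outcome is fixed for each person and is known only after the EMA period has ended.

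Part of the stated primary goal of phase 2 is to identify real-time factors that predict adherence. If the analysis is run as written, a daily factor such as affect or digestive symptoms would show no effect even if it strongly drove fiber intake, and that result could be read as evidence of no effect. The power statement also leads the reader to expect the precision of several hundred observations, when the stated outcome supplies at most 64.

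**Working it through.** **1. The plan's own figure.** Inputs from the Power section: 64 participants, 28 days, 75% compliance, correlation 0.7.
- Responses: 28 × 0.75 = 21 per person; 64 × 21 = 1344.
- Effective sample size, first-order autoregressive form: 1344 × (1 − 0.7)/(1 + 0.7) = 237.2. This reproduces 237. The literal product 0.7 × 1344 = 941 does not, nor does an exchangeable correlation, 1344/(1 + 20 × 0.7) = 89.6.
- Power for f²=0.034: noncentral F with 1 and 235 df, noncentrality 0.034 × 237 = 8.06, two-sided alpha 0.05 (assumed; the article gives none) = 80.7%. This agrees with the stated 80%.

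The figure is therefore sound for an outcome measured at every diary. The next steps ask what happens with the outcome actually defined.

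**2. Number of outcome values.** The start recall supplies the reference and the end recalls supply the comparison, so there is one status y_i per participant and at most 64 in all. Scoring the two end recalls separately would give at most two values per person, both after the EMA period.

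**3. Daily-deviation main effect.** Let d_it be participant i's deviation from their own mean on row t, so Σ_t d_it = 0. With y_i the same on every row, the score for the deviation coefficient b, evaluated at b = 0, is Σ_i (y_i − p_i) Σ_t d_it = 0. The log-likelihood is concave in b, so b = 0 is the maximum. Given any value of the random intercept the same holds, so integrating over the intercept does not change it. In 500 simulated data sets (64 × 21 rows, logistic fit), the largest |b| was about 3 × 10⁻¹⁶.

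**4. Random intercept.** With identical outcomes on all 21 rows of a participant and 41 of 64 adherent (assumed), the log-likelihood maximized over the intercept is:
- SD 1: −310.1
- SD 10: −61.4
- SD 100: −43.5
- SD 500: −42.1

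The limit is the likelihood of 64 single observations: 41 ln(41/64) + 23 ln(23/64) = −41.8. The log-likelihood keeps rising towards that limit, so there is no finite estimate of the SD. With 38 of 64 adherent the pattern is the same: −88.0 at SD 5, −52.8 at SD 20, −44.4 at SD 160, limit −43.2.

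**5. A fallback the plan does not state.** If the status were copied to every row and clustering ignored, a participant-mean predictor with no true effect would be significant in about 67% to 70% of simulated data sets (adherence about 0.6 assumed), against about 5% with one row per participant.

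**6. Power with 64 outcomes.** For f²=0.034 the noncentrality is 0.034 × 64 = 2.18 and power is about 31%; 80% power needs f² of about 0.127. For a single-level logistic model, the odds ratio per SD detectable with 80% power is exp[(1.960 + 0.842)/√(64 p(1 − p))], where p is the adherence rate. The article gives no rate, so as a range: 2.0 at p = 0.5, 2.1 at 0.3 or 0.7, and 2.4 at 0.8.

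**The case against.** A reader might infer that nothing in phase 2 can work. The document does not support that, for four reasons.

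- **Participant-level predictors.** The EMA mean and the within-person SD, both in the Analytic Plan, are legitimate predictors of a participant-level status. They can be estimated on about 64 people. Describing whether participants maintain intake is also unaffected.
- **Time-varying effects.** It is tempting to say that these need an outcome that changes over time. They do not. Whether stress late in the period predicts end status more than stress early on is a well-defined question with one outcome per person. In a simulation of 64 participants over 28 days, using a deviation-by-time term and cluster-robust errors, type I error was 4.0%. Power was 18% and 35% for log-odds of 1 and 2 per unit of week-4 mean stress. Such an analysis is feasible but weak, it compares people only, and the article does not describe it in those terms.
- **The 67% to 70% false-positive rate.** The article plans a multilevel model. It nowhere says that rows are copied or clustering ignored, so this rate is not the error of the planned analysis.
- **Importance.** The primary outcome of the study is feasibility, and phase 1 does not use this model.

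What remains is the incompatibility itself. The article fixes both the outcome and the model, so further detail in an analysis plan cannot reconcile them without changing one. Nor can one suppose that the daily checklist was meant, because adherence is tied expressly to ASA-24.

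**Conclusion.** The point holds in a limited form. The stated outcome has one value per participant. For that outcome the daily-deviation main effect is zero by algebra, and a random intercept has no finite variance estimate if the status is carried on every EMA row. Both results hold whatever the adherence rate, provided both statuses occur; the likelihood values shown assume 38 or 41 of 64 adherent. A time-varying model remains possible only as a between-person analysis.

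The power statement reproduces but belongs to a different, repeated outcome. For the binary status with 64 participants, power at f²=0.034 falls from about 81% to about 31%, with two-sided alpha of 0.05 assumed and the same linear-model effect size used as a guide. Participants without end recalls would lower it further. The wider inferences, that phase 2 fails altogether or that it would produce mostly false positives, do not follow from the text.

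**What to change.** 1. **ASA-24 maintenance.** Analyze with one row per participant: Firth logistic regression for the 0/1 status, or a linear model of end-to-start fiber intake. Use EMA means and SDs as predictors. Describe any early-versus-late analysis of this outcome as between-person.
2. **Daily factors and within-person time-varying effects.** Name the morning-diary high-fiber checklist as the repeated outcome in the multilevel and time-varying models, with person-mean and within-person-centered predictors. Pair each day's predictors with the checklist that covers that day's intake. The diary comes before typical morning mealtimes, so this would be the next morning's diary if the checklist asks about the previous day. The article does not state the recall window, and the plan should.
3. **Power.** Restate it separately for each outcome.

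**Cost.** No new data collection is needed, and enrollment was only slated to begin in April 2026. There are three downsides:
- The checklist is a different and cruder estimand than grams from ASA-24, and it has no reference level or threshold yet.
- Lagged pairing needs both diaries. If missingness is independent, 27 × 0.75² = 15.2 day pairs per person remain, or about 64 × 15.2 = 972 in all, instead of 1344 responses.
- The stated power for the ASA-24 outcome becomes less favorable.
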